### Costs

We will conduct activity-based costing and time and motion observation in all three study arms to estimate the incremental cost of implementing EUC, SPI, and TCBT-S. Throughout study implementation, we will estimate all costs that would be incurred by the Ministry of Health to administer the EUC, SPI, and TCBT-S interventions. These costs will be collected and tabulated using activity-based cost menus during start-up and trial implementation. Costs include screening, youth counseling sessions, emergency referrals, personnel, supervision, supplies, buildings and overhead, intervention delivery, training, and equipment. Time-motion observations following protocols previously used by our group in Mozambique [73] will estimate personnel time needed for EUC, SPI, and TCBT-S tasks.

### Economic evaluation

We will parameterize the model with costs and primary/secondary outcome data from the trial to simulate the health and economic impacts of scaling-up EUC, SPI alone, or TCBT-S in Mozambique at district, provincial, and national levels. Health outcomes include effects on suicidal behavior, suicidal ideation, and depression. The model will estimate the effects of scale-up scenarios on: (1) suicidal behavior; (2) suicidal ideation; (3) depressive symptoms; and (4) Disability Adjusted Life Years (DALYs) [74] averted; (5) cost per DALY averted; and (6) budgetary impact from the payer (Ministry/Mozambican Government) perspective. Different scenarios will examine rate and breadth of expansion (number/characteristics of future schools/districts/provinces). We will estimate incremental costs, as well as treatment costs incurred and averted due to SPI alone and TCBT-S. Throughout study implementation, all payer costs (MoH) will be collected and tabulated using activity-based cost menus to collect cost at start-up, implementation, and scale. Costs include but are not limited to: student visits; hospitalization; medication; personnel; supervision; supplies; buildings and overhead; intervention delivery; training; equipment; and any school resources utilized whether direct or in-kind. Time-motion observations following protocols previously used by our group in Mozambique [73] will estimate personnel time needed for EUC, SPI, and TCBT-S intervention implementation.

We will develop a Markov cohort model using R software reflecting the natural history of suicidal behavior, suicidal ideation, and depression progression and disability under different treatment scenarios. Similar Markov models have been used for previous cost-effectiveness analyses of suicide prevention and mental health interventions globally [75–84]. The model simulates a cohort of students stratified by types of suicidal ideation, behavior, death, and depression. The model will be parameterized with cost and outcome data from EUC/SPI/TCBT-S and school-level contextual data (location; size; type) and demographic data (grade; gender; age distributions). In line with previous studies and economic guidelines [74, 75], costs and effectiveness will be discounted at 3% annually (varied from 0–5% in sensitivity analyses). Disability weights for DALYs will be obtained from the Global Burden of Disease 2019 [85, 86]. Scale-up scenarios will model changes in rates of suicidal behavior, ideation, and depression based on study results and varied in sensitivity analyses. Prior to conducting cost-effectiveness analyses we will assess model validity/reliability by evaluating our model’s ability to accurately project trends in suicidal behavior.

We will project effects of SPI and TCBT-S on suicidal behavior, ideation, and depression compared to EUC. We will calculate the costs per suicidal behavior averted and the Incremental Cost-Effectiveness Ratio (ICER) per suicidal behavior averted and DALYs averted for each scale-up scenario. Following WHO guidelines [87–89], SPI alone or TCBT-S will be considered cost-effective if the ICER is less than Mozambique’s gross domestic product per capita. Analyses will be from the payer perspective, using economic productivity data to estimate disability averted and incorporating costs of healthcare assess. We will also estimate the budget impact, including costs incurred and averted, disaggregated by category to inform planning.

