**Discussion:**

This study is innovative in being the first, to our knowledge, to rigorously test SPI and TCBT-S for adolescent suicide prevention in Sub-Saharan Africa. By simultaneously testing the brief SPI alone – as well as integrated into a more resource-intensive TCBT-S – this study will examine whether the potential gains in effectiveness with the more resource intensive TCBT-S justify its scale-up versus the brief SPI intervention. If effective, SPI or TCBT-S have a large potential to be rapidly scaled up to safeguard youth mental health in Mozambique and other similar LMICs.

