The Common Elements Treatment Approach—Mozambique (CETA-MZ) CBT-based transdiagnostic therapy is feasible, acceptable, and associated with decreases in depressive symptoms and suicidal ideation in Mozambique. Starting in 2018, our team led the adaptation of CETA to the Mozambican context. This included training/supervision of non-specialist healthcare workers and a demonstration project to test feasibility, acceptability, and clinical outcomes among patients testing HIV + in primary care clinics of Sofala, Mozambique. Initial data suggested that, among youth 18–24, CETA-MZ was associated with an 80% reduction in depression symptoms and a reduction in suicidal ideation from 20% at intake to < 3% after 5 sessions [21]. CETA and other cognitive behavioral interventions have also been tested in other contexts showing feasibility, acceptability, and effectiveness among youth < 18 and in schools [22–26].

We believe that these two evidence-based practices, both with demonstrated feasibility in Mozambique, have the potential to be powerful interventions to prevent adolescent suicidal behavior. Yet, a recent meta-analysis found lower comorbidity of psychiatric disorders and suicidal behavior in LMICs (~ 50%) compared to high-income countries (~ 90%) [27]. Therefore, it is possible that applying CETA-MZ to address psychiatric symptoms may not lead to significant decreases in suicidal behavior above and beyond SPI alone. For these reasons, we propose to test both SPI alone and the integration of SPI into CETA-MZ – adapted for adolescent suicide prevention – to create a Transdiagnostic Cognitive Behavioral Therapy for Suicide (TCBT-S) delivered by non-specialists in Mozambican secondary schools. Due to limited resources for mental health in the African region we aim to test whether the potential gains in effectiveness with the more resource intensive TCBT-S justify its scale-up versus the brief SPI intervention alone. This study will be conducted using a three-arm parallel Hybrid Type-1 cluster randomized trial design across 21 schools (7 to each arm of Enhanced Usual Care [EUC], SPI alone, and TCBT-S). This study will also generate evidence on costs, implementation determinants, and potential mechanisms of intervention effects to optimize intervention components and implementation strategies for future scale-up, if effective.

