### Primary statistical analyses

Individual-level primary and secondary outcome data will be analyzed using generalized linear mixed models using the binomial family, logit link, and random effects at the school and individual level. Primary analyses will compute odds ratios for suicidal behavior in the past month comparing the SPI alone and the TCBT-S arms to EUC; primary outcome analyses will be done at 6 months post intake. We will also conduct supplementary analyses of primary and secondary outcomes at 3 months post intake. Sensitivity analyses will utilize gaussian models to directly compute differences in the proportion of SPI and TCBT-S with suicidal behavior compared to EUC. Student (age, sex, grade) and school (size, location) will be considered for inclusion based on balance. Secondary analyses will utilize the same modeling approaches to evaluate odds ratios for suicidal ideation and PHQ-9 ≥ 10 as well as directly comparing outcomes between SPI alone and TCBT-S arms. We will also examine absolute differences in PHQ-9-MZ scores across groups using gaussian models. Sex as a biological variable will be assessed using pre-specified interaction sub-analyses to examine differential SPI and TCBT-S effects for females vs. males. For the RE-AIM maintenance domain, we will repeat all analyses at 12 and 24 months. All statistical analyses will be conducted blinded to study arm.

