### Primary study power assessment

A 2021 meta-analysis of 6 studies of suicide safety planning interventions in high-income contexts found a global relative decrease in SB of 43% (RR: 0.57; 95% CI: 0.41–0.79). Using a conservative alpha value of 0.025 to account for multiple comparisons in the 3-arm cRCT design, an ICC of 0.02, estimated average cluster size of 100 students expressing active SI (14% of 14,788 students screened), we will have > 80% power for a conservative relative decrease in SB of 35%. This represents an absolute difference of 13%, with an estimated 37% of control students with SB in the past month compared to 24% in the intervention groups. See Table 4 for power under varying effect estimates and mean number of students with active SI. Currently there is no consensus in the statistical literature on whether three-arm cRCTs should adjust their alpha value for multiple comparisons with a concurrent control group; half of published trials have adjusted for multiple comparisons and half have not adjusted [50, 51]. Since our two arms are testing a related treatment (SPI alone versus TCBT-S) we argue that more stringent control of family-wise error rate should be employed. Thus, we have chosen to use the conservative Bonferroni correction to account for multiple comparisons in our primary outcome assessment (Alpha = 0.05/N primary outcome tests = 0.025). If we employ an alpha of 0.05, we will have > 80% power to detect a relative decrease of 32.5% (an absolute difference of 12%).

**Table 4 Tab4:** Power under various conditions. Green indicates power > 80%

Mean number of students with active SI per school						
**Primary Outcome:** Decrease in Suicidal behavior in past month from 37% (p1-p0)		60	80	100	120	140
	12.5%	.67	.72	.76	.79	.81
	15%	.84	.89	.92	.93	.94
	17.5%	.95	.97	.98	.99	.99
	20%	.98	>.99	>.99	>.99	>.99

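### The cost-effectiveness rule names no TCBT-S versus SPI ICER, though that is the question the trial asks, and does not say which of two ICERs faces the GDP threshold

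*Protocol article*

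**What the plan says.** All references are to the protocol article.

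- **The question.** The Background states: "we aim to test whether the potential gains in effectiveness with the more resource intensive TCBT-S justify its scale-up versus the brief SPI intervention alone". The abstract's Discussion repeats it, saying the study will examine "whether the potential gains in effectiveness with the more resource intensive TCBT-S justify its scale-up versus the brief SPI intervention".
- **The nesting.** The section specifying TCBT-S explains that the whole of SPI is built into it, with the safety plan made at first contact and revisited at later visits.
- **The comparator.** Economic evaluation says: "We will project effects of SPI and TCBT-S on suicidal behavior, ideation, and depression compared to EUC". No other comparator is named in that section.
- **The ratios.** The next sentence announces the "Incremental Cost-Effectiveness Ratio (ICER) per suicidal behavior averted and DALYs averted for each scale-up scenario". These are two ratios with different denominators.
- **The rule.** The sentence after that reads: "SPI alone or TCBT-S will be considered cost-effective if the ICER is less than" Mozambique's GDP per capita.
- **The head-to-head.** Primary statistical analyses includes, among secondary analyses, "directly comparing outcomes between SPI alone and TCBT-S arms". This concerns clinical outcomes and does not mention costs or ICERs.

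**The concern.** There are two separate faults.

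The first is the comparator. With three strategies, one nested in another, whether the richer package is worth its price depends on what it adds over the cheaper one. A ratio of TCBT-S to EUC averages SPI's gains together with whatever the CBT modules add. If SPI is cheap and does most of the work, that average can look good while the additional spending buys little. The Background itself raises the possibility that treating psychiatric symptoms may not reduce suicidal behavior beyond what SPI achieves, which is exactly the case in which this rule misleads. Both arms can pass, and the rule then leaves the stated question unanswered.

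The second is the denominator. The rule refers to a single ICER just after two have been defined. GDP per capita can serve as a yardstick for the cost of a unit of health such as a DALY. It has no defined meaning as a price per suicidal behavior averted. The two ratios coincide only if each behavior averted is worth exactly one DALY.

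**Working it through.** The plan gives no cost, DALY or GDP figure, so there is no economic figure to reproduce. The check is whether the rule as printed and an incremental rule can disagree, and over what range.

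**Inputs from the document.** The power section gives "an estimated 37% of control students with SB in the past month compared to 24% in the intervention groups". For SPI, E_S = 0.37 − 0.24 = 0.13 behaviors averted per student.

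**Assumed inputs.**
- Cost over EUC per student, in units of GDP per capita: C_S = 0.02 for SPI and C_T = 0.06 for TCBT-S.
- Suicidal behavior under TCBT-S: varied from 24% to 17%.
- DALYs averted per behavior averted, k: varied from 0.5 to 5.
- Threshold L = 1 GDP per capita per DALY.

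Treating a past-month prevalence difference as behaviors averted, and tying DALYs to behavior alone, are simplifications. DALYs gained through ideation or depression are left out.

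**Formulas.**
- Against EUC: C_T / (k × E_T)
- Against SPI: (C_T − C_S) / [k × (E_T − E_S)]

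With E measured in DALYs, the two rules conflict whenever C_T < L × E_T and C_T − C_S > L × (E_T − E_S).

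**Varying the TCBT-S rate (k = 1).** SPI against EUC is 0.02/0.13 = 0.15, a pass.

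| TCBT-S rate | E_T | TCBT-S vs EUC | TCBT-S vs SPI |
|---|---|---|---|
| 24% | 0.13 | 0.06/0.13 = 0.46 | no added benefit at higher cost: SPI dominates |
| 23% | 0.14 | 0.06/0.14 = 0.43 | 0.04/0.01 = 4.00 |
| 22% | 0.15 | 0.06/0.15 = 0.40 | 0.04/0.02 = 2.00 |
| 20% | 0.17 | 0.06/0.17 = 0.35 | 0.04/0.04 = 1.00 |
| 17% | 0.20 | 0.06/0.20 = 0.30 | 0.04/0.07 = 0.57 |

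TCBT-S passes against EUC in every row. Against SPI it passes only when it lowers the rate by more than a further 4 points (0.04/1), that is, to below 20%. The first row uses the power section's 24% for both intervention groups. That is a planning value and not a forecast that the arms will be equal.

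**Varying k (TCBT-S rate 22%).**

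| k | TCBT-S vs EUC | TCBT-S vs SPI |
|---|---|---|
| 0.5 | 0.80 | 4.00 |
| 1 | 0.40 | 2.00 |
| 2 | 0.20 | 1.00 |
| 5 | 0.08 | 0.40 |

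The conflict is gone at k = 5.

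**Denominator.** Take k = 0.5, C_T = 0.10 and a TCBT-S rate of 22%, against EUC. Per behavior averted: 0.10/0.15 = 0.67, a pass. Per DALY averted: 0.10/(0.5 × 0.15) = 1.33, a fail. The same data give opposite verdicts depending on which ICER is read.

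**The case against.** The strongest reply is that the rule sentence names no comparator. EUC appears two sentences earlier, attached to projected effects. Other wording is neutral: Study aims speaks of the incremental cost and cost-effectiveness of scaling up both interventions, Costs covers all three arms, and Economic evaluation simulates EUC, SPI alone and TCBT-S as three strategies. Nothing rules out a TCBT-S versus SPI ICER, and the article condenses a fuller plan. This stands in part: the text does not expressly say that each ICER is against EUC, and a reader who takes it that way is inferring. But EUC is the only comparator the section names, the rule judges each arm singly, and the incremental contrast that the stated aim calls for appears nowhere in the economic text. That is a mismatch between a printed rule and a printed aim, and more than omitted detail.

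On the denominator, a reader might infer that the threshold is applied to both ratios. The text does not say so, because it refers to one ICER. The only cost ratio in the list of model outputs is cost per DALY averted, so a per-DALY reading is plausible. What remains is an ambiguity that a few words would remove.

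A reader might also infer that the rule would recommend national scale-up of TCBT-S. The documents do not support that. The rule only labels an arm cost-effective, and budget impact and scale-up scenarios are reported beside it.

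Finally, the costs, the DALY values and the TCBT-S rates in the working are assumed. They show that the conflict can arise, not that it will.

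**Conclusion.** The point holds in limited form. As printed, the economic section offers no test of TCBT-S against SPI, although the abstract and Background make that the question. The rule can label TCBT-S cost-effective when its ICER against SPI exceeds the same threshold, or when SPI dominates it. Under the assumed costs and k = 1, TCBT-S against EUC lies between 0.30 and 0.46 GDP per capita per DALY across rates of 17% to 24%. Against SPI it runs from 0.57 at 17% to 4.00 at 23%, and TCBT-S is dominated at 24%. The conflict vanishes if the added benefit, or the DALYs per behavior averted, are large. The unspecified denominator is a second, independent ambiguity.

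This should be fixed, but it does not threaten the trial. It concerns a modelling aim, leaves the primary outcome, randomization and data collection untouched, and can be corrected at any time before the economic analysis.

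**What to change.** Amend the decision rule in Economic evaluation to state that:

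1. ICERs are computed incrementally after removing dominated options: SPI against EUC, then TCBT-S against SPI.
2. TCBT-S is judged on its ICER against SPI, or against the next cheaper non-dominated option if SPI is itself dominated. Its ratio to EUC may be shown but does not decide.
3. The GDP-per-capita threshold applies to cost per DALY averted only. Cost per suicidal behavior averted is reported descriptively, with no threshold.

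The cost is a few sentences and one further contrast from the same Markov model. Costs and outcomes are already to be collected in all three arms, so no new data are needed.

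### The payer-perspective economic evaluation estimates disability averted from productivity data without reconciling this with its Global Burden of Disease weights, so the ICER judged against GDP per capita is not consistently defined

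*Protocol article*

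**What the plan says.** All the relevant text is in the Costs and Economic evaluation sections of the protocol article.

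- **Perspective and productivity:** "Analyses will be from the payer perspective, using economic productivity data to estimate disability averted".
- **DALY weights:** "Disability weights for DALYs will be obtained from the Global Burden of Disease 2019".
- **Payer:** the budget output is described as "budgetary impact from the payer (Ministry/Mozambican Government) perspective", and the Costs section says "we will estimate all costs that would be incurred by the Ministry of Health".
- **Cost items:** these are service-delivery items such as visits, hospital care, drugs, staff, training, equipment and school resources. The list in Economic evaluation is open-ended but is headed as payer (Ministry of Health) costs. The only saving named is avoided treatment cost. Productivity is in neither section's list.
- **Result and rule:** the plan will report the "Incremental Cost-Effectiveness Ratio (ICER) per suicidal behavior averted and DALYs averted for each scale-up scenario", and "SPI alone or TCBT-S will be considered cost-effective if the ICER is less than Mozambique’s gross domestic product per capita".

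The sentence under perspective is the only place in these two sections where productivity data appear.

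**The concern.** Two things do not fit together.

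First, students' lost or regained output generally falls on individuals and on society, not on a Ministry budget. A productivity input therefore sits badly with the declared perspective and with a costing exercise limited to payer costs.

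Second, disability averted is a component of DALYs averted. The section gives it two bases, GBD weights and productivity data, and does not say whether the second replaces the first, adds to it or stands apart from it.

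This matters because the plan fixes a pass/fail rule. The numerator and denominator of the ICER must both be settled before that rule can be applied. As the text stands, an analyst could choose the role of productivity after seeing the results, and that choice could decide whether SPI alone or TCBT-S is called cost-effective. The article expects its findings to inform scale-up and policy.

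**Working it through.** **No figure to reproduce.** The article gives no ICER, DALY total, GDP amount or productivity value. The check is therefore algebra on the decision rule, with GDP per capita left as a symbol.

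**Inputs**
- G = GDP per capita. The threshold is 1 × G (Economic evaluation); the amount is not given.
- C = incremental payer cost.
- D = DALYs averted using GBD 2019 weights.
- f, g, k = unknown roles for productivity. These are assumptions, shown over a range.
- The rule is read as applying to the cost per DALY. Discounting (3%, varied from 0 to 5%) does not affect the algebra, because C and D are taken as already discounted.

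**Base case: productivity outside the ICER.** The rule is C/D < G. The highest passing payer cost per DALY is 1.00 G.

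**Reading A: productivity worth f × G per DALY is netted from cost.** (C − f·G·D)/D < G, so C/D < (1 + f)·G.

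| f | Highest passing C/D |
|---|---|
| 0 | 1.00 G |
| 0.25 | 1.25 G |
| 0.5 | 1.50 G |
| 0.75 | 1.75 G |
| 1 | 2.00 G |
| 1.5 | 2.50 G |

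**Reading B: productivity is converted to extra DALYs, a fraction g of D.** C/[D(1 + g)] < G, so C/D < (1 + g)·G. This gives 1.25 G at g = 0.25, 1.50 G at g = 0.5 and 2.00 G at g = 1.

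**Reading C: a productivity-based measure replaces the GBD-weighted one, at ratio k.** C/(k·D) < G, so C/D < k·G.

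| k | Highest passing C/D |
|---|---|
| 0.5 | 0.50 G (stricter) |
| 0.75 | 0.75 G (stricter) |
| 1 | 1.00 G (unchanged) |
| 1.5 | 1.50 G (laxer) |
| 2 | 2.00 G (laxer) |

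**Two hypothetical interventions** show that the verdict could move either way.
- With C/D = 1.4 G, the base case fails. Reading A at f = 0.5 gives 1.4 G − 0.5 G = 0.9 G, which passes.
- With C/D = 0.7 G, the base case passes. Reading C at k = 0.5 gives 0.7 G / 0.5 = 1.4 G, which fails.

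The text does not say which reading is meant. Readings B and C follow its wording most closely, because it ties productivity to estimating disability. Reading A needs a cost credit that the text does not mention.

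**The case against.** The strongest reply is that this is one loosely edited sentence in a condensed article. The DALY weights are plainly assigned to GBD 2019. The later phrase speaks of disability averted, not DALYs, and could mean a supplementary valuation reported beside the ICER. The same sentence contains another slip, in its closing words on healthcare costs. How productivity enters a Markov model is detail that a full economic plan would normally hold.

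Part of this stands. The two bases for disability are unreconciled rather than proven incompatible, and if productivity is only a side result the ICER is unaffected. But the point is not that detail is missing. The sentence states a method, under a declared payer perspective, that fits neither the payer costs listed nor the DALY source named. Further detail elsewhere would still leave it needing correction.

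A reader might go further and infer that health gains are counted twice, that the bar is effectively halved, or that a failing intervention would be turned into a passing one. The documents do not support this. Nowhere do they say that productivity gains are given a money value, subtracted from cost or added to DALYs. A factor of two needs exactly f = 1 or g = 1 (or k = 2 under replacement), each one point in an undocumented range, and replacement could instead tighten the test. Nor can the two complaints be merged: if productivity data and GBD weights are rival sources for one quantity, only one is used and nothing is counted twice.

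**Conclusion.** The point holds as an inconsistency in how the ICER is defined. The plan declares a payer perspective and names GBD weights, then brings in productivity data for disability averted without saying how they enter. The quantity compared with GDP per capita is therefore not fixed.

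Neither size nor direction can be derived from the documents. Over the assumed ranges, the highest passing payer cost per GBD-weighted DALY runs from 0.5 G (replacement at k = 0.5) to 2.5 G (netting at f = 1.5). It stays at 1.0 G if productivity is kept out. The nominal threshold is G throughout; what moves is the payer cost per DALY that it admits.

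This should be corrected, but it concerns the secondary economic aim only. The primary effectiveness analysis is untouched.

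**What to change.** Rewrite the one sentence in Economic evaluation. Define the base-case ICER compared with GDP per capita as incremental payer costs, net of averted treatment costs, divided by DALYs averted using GBD 2019 weights only. Then do one of two things:

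- delete the productivity clause; or
- keep productivity as a separately labelled societal-perspective scenario, and state that it does not enter the payer ICER.

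The change needs no new data and no change to trial conduct. Its downside is that the base-case ICER may look less favourable than one that credits productivity.
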